## Abstract

Around 14% of pregnancies globally are affected by gestational diabetes mellitus (GDM), making it one of the most common disorders experienced by women in pregnancy. While dietary, physical activity and supplement interventions have been implemented to prevent GDM, with varying levels of success, altering the gut microbiota through diet is a promising strategy for prevention. Several studies have demonstrated that women with GDM likely have a different gut microbiota to pregnant women without GDM, demonstrating that the gut microbiota may play a part in glycemic control and the development of GDM. To date, there have been no randomized controlled trials using diet to alter the gut microbiota in pregnancy with the aim of preventing GDM. Here, we present the study protocol for a single-blind randomized controlled trial which aims to determine the effectiveness of the *Healthy Gut Diet* on reducing the diagnosis of GDM in pregnant women with one or more risk factors. Consenting women will be randomized into either the *Healthy Gut Diet* intervention group or the usual care (control) group after 11 weeks gestation. The women in the intervention group will receive three telehealth counseling appointments with an Accredited Practicing Dietitian with the aim of educating and empowering these women to build a healthy gut microbiota through their diet. The intervention was co-designed with women who have lived experience of GDM and incorporates published behavior change techniques. The control group will receive the usual care and will also be shown a brief (3 min) video on general healthy eating in pregnancy. The primary outcome is the diagnosis of GDM at any stage of the pregnancy. Secondary outcomes include changes to gut microbiota composition and diversity; gestational weight gain; maternal and infant outcomes; management of GDM (where relevant); dietary quality and intake; physical activity; and depression scoring. We aim to recruit 120 women over 16 months. Recruitment commenced in January 2023. The trial has been registered with the Australian New Zealand Clinical Trials Registry (ACTRN12622001285741).

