## 1. Introduction

Gestational diabetes mellitus (GDM) is a common and costly condition that occurs during pregnancy. Globally, the prevalence of GDM is estimated to be around 14% [1]. In Australia, GDM incidence has doubled in the decade since 2010 and affects one in six Australian pregnancies [2,3]. Although much of this increase has been due to changes to the diagnostic criteria, certain risk factors increase the risk of developing GDM [4]. Up to 70% of women with GDM will develop it again in subsequent pregnancies [5]. The effects of GDM are intergenerational. Women with GDM have a 10-fold increased risk of type 2 diabetes [6] and a 2-fold risk of cardiovascular events [7]. Their children are more likely to develop cardiometabolic conditions and to experience obesity [8].

Medical nutrition therapy and physical activity, together with self-monitoring of blood glucose levels, are the cornerstone of GDM management; however, around 50% of women will require pharmacological intervention in the form of oral hypoglycemic agents or insulin [9]. Strong predictors of GDM include early excess gestational weight gain (GWG), a pre-pregnancy body mass index (BMI) above 25 kg/m^2^, and a history of GDM [5,10,11]. Several studies have demonstrated a positive effect of dietary intervention for the prevention of GDM [12] but have not consistently shown reductions in GDM risk [13].

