#### 2.9.2. Intervention Procedures

Following consent and enrolment, women are sent a link to book a telehealth appointment with the intervention dietitian. Ideally, the first appointment (approximately 45 to 60 min in length) is attended within 1 to 2 weeks of enrolment and must occur before 18 weeks gestation (but not before 12 weeks gestation). Intervention content and procedures are outlined in Supplementary Table S1: Item 2. Women are encouraged to set three dietary behavior goals at the initial appointment, in alignment with the three Healthy Gut Diet recommendations. At each follow-up, progress towards the goals is reviewed with the dietitian and revised where necessary. For intervention fidelity, each appointment will follow a pre-defined script with a fidelity checklist to ensure all participants receive the same information. The study lead, also an Accredited Practicing Dietitian, randomly selects two counseling sessions per month to attend as an observer to further assess fidelity of intervention delivery.

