### 2.13. Statistical Methods

The study results will be reported as per the Consolidated Standards of Reporting Trials (CONSORT) guidelines [37]. Results will be reported using an intention-to-treat approach, so all women in the intervention arm will be included in the primary analysis. In a sensitivity analysis, a per protocol approach will be used. Data from women who did not complete at least two of the three dietary counseling sessions will be excluded from this analysis. For the primary outcome (Section 2.13.1), comparisons between the groups using the binary outcome of GDM or no GDM diagnosis will be conducted using chi-square analysis. Logistic regression models will be used to adjust for potential confounders, decided a priori using causal diagrams. Confounders will include age, parity, pre-pregnancy BMI (categorical), weight gain above the Institute of Medicine recommendations based on pre-pregnancy BMI [38], assisted conception, and antibiotic use.

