#### 2.13.5. Health Outcomes

Relevant pregnancy and infant outcomes include gestational age at delivery, mode of delivery, preterm birth, pregnancy-induced hypertension, polyhydramnios, edema, large-and-small-for-gestational age, neonatal hypoglycemia, and admission to a special care nursery.

Gestational weight gain recorded in medical records (and cross-referenced against self-reported weight at the 36-week survey) will be calculated by subtracting pre-pregnancy weight from the last recorded pregnancy weight. Gestational weight gain will also be classified as above, below, or within recommendations according to the Institute of Medicine cut-offs [38] based on pre-pregnancy body mass index.

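### The adjusted logistic model for GDM treats gestational weight gain as a confounder, although it accrues largely after randomisation and may mediate the diet's effect

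*Protocol article*

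**What the plan says.** Section 2.13 sets out two analyses of the primary outcome under an intention-to-treat approach. First, "comparisons between the groups using the binary outcome of GDM or no GDM diagnosis will be conducted using chi-square analysis". Second, "Logistic regression models will be used to adjust for potential confounders, decided a priori using causal diagrams". The named covariates are age, parity, pre-pregnancy BMI, and "weight gain above the Institute of Medicine recommendations based on pre-pregnancy BMI [38], assisted conception, and antibiotic use".

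Section 2.13.5 says that gestational weight gain "will be calculated by subtracting pre-pregnancy weight from the last recorded pregnancy weight", with a cross-check against self-reported weight at the 36-week survey. It is then classified against the same Institute of Medicine cut-offs that Section 2.13 uses for the covariate.

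Weight gain has other roles in the article:
- Abstract: "Secondary outcomes include changes to gut microbiota composition and diversity; gestational weight gain".
- Introduction: "Strong predictors of GDM include early excess gestational weight gain (GWG").
- Discussion, closing paragraph: weight gain inside the recommended range is listed among the possible benefits of the trial's approach.

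**The concern.** A confounder of a treatment comparison must be a cause, or a marker of a cause, of treatment assignment. Here assignment is random, so a variable that develops after assignment cannot be one. Adjusting for it changes what is estimated.

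- If the diet lowers GDM risk partly by limiting weight gain, adjustment removes that part of the benefit.
- If a GDM diagnosis changes later weight gain, or if an unmeasured factor drives both weight gain and GDM, adjustment can produce an association with allocation where the diet does nothing.

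The article gives two results for the primary outcome and does not say which takes precedence. In a trial of 120 women, readers may lean on the adjusted odds ratio. The Discussion also intends the pilot to inform later sample-size calculations, so a distorted odds ratio could carry forward.

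**Working it through.** The article states no figure for this point, so the main check is the order of events.

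1. **Allocation.** Women are randomised after 11 weeks (Abstract) and must enrol before 18 weeks (Section 2.3). The first dietitian session "must occur before 18 weeks gestation (but not before 12 weeks gestation").
2. **Weight gain.** It runs from before pregnancy to the last recorded weight. Taking 36 weeks as a reference for that weight (an assumption based on the survey used as cross-check), the time after allocation is 36 − 18 = 18 weeks to 36 − 11 = 25 weeks. That is 50% to 69% of the 36 weeks.
3. **Diet to weight gain.** The Abstract and Discussion treat weight gain as an outcome of the trial.
4. **Weight gain to GDM.** The Introduction supports this for early excess gain.
5. **GDM to later weight gain.** The Introduction says GDM is managed with nutrition therapy and physical activity. That such management changes later gain is an inference.

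Steps 1 to 4 make the covariate a potential mediator. Step 5 makes it possibly a consequence of the outcome. A causal diagram drawn from these statements would not place it among the confounders.

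To see what adjustment can do, 2,000,000 women per scenario were simulated. All coefficients are assumed; none comes from the article. T is allocation (1:1), E is early excess gain, F is final excess gain, and U is an unmeasured standard normal factor:

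- logit P(E) = −0.2 + a·T + u·U
- logit P(GDM) = −1.0 + d·T + b·E + u·U
- logit P(F) = −1.2 + 2.4·E + a·T + c·GDM + u·U

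The adjusted model contains T and F. The shift is ln(adjusted OR) − ln(unadjusted OR).

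| Scenario | d | a | b | c | u | Unadjusted OR | Adjusted OR | Shift |
|---|---|---|---|---|---|---|---|---|
| Effect only through early gain | 0 | −0.7 | 0.8 | 0 | 0 | 0.874 | 0.954 | +0.088 |
| Same, and GDM lowers later gain | 0 | −0.7 | 0.8 | −1.0 | 0 | 0.878 | 0.825 | −0.062 |
| Direct effect plus early gain | −0.4 | −0.7 | 0.8 | 0 | 0 | 0.593 | 0.645 | +0.084 |
| No effect on GDM; GDM lowers later gain | 0 | −0.7 | 0 | −1.0 | 0 | 1.005 | 0.880 | −0.133 |
| No effect on GDM; shared unmeasured cause | 0 | −0.7 | 0 | 0 | 1.0 | 1.002 | 1.157 | +0.144 |
| Direct effect; neither diet nor GDM alters gain | −0.7 | 0 | 0.8 | 0 | 0 | 0.512 | 0.508 | −0.008 |

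The shift goes in both directions. It is negligible only where neither allocation nor GDM affects weight gain.

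For scale, with 60 women per arm and a common risk p, the standard error of the log odds ratio is √(2 / (60·p·(1 − p))). At p = 0.27 it is √(2 / 11.83) = 0.41, and at p = 0.303 it is √(2 / 12.67) = 0.40. The two null scenarios therefore shift the estimate by 0.133 / 0.41 = 0.32 and 0.144 / 0.40 = 0.36 standard errors.

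**The case against.** Five points can be made for the plan.

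- **The chi-square comparison uses no covariates.** This stands. A reader might infer that the trial has no valid analysis of its primary outcome. The article does not support that, because the unadjusted intention-to-treat comparison is untouched. It does not, however, repair the adjusted estimate.
- **Antibiotic use sits in the same list.** A reader might infer that it is a post-randomisation covariate too. Section 2.13 gives no time window, and Section 2.11 collects antibiotic intake at baseline as well as at 36 weeks. Use during pregnancy is specified only for the microbiota sensitivity analysis in Section 2.13.4. The article gives no reason to expect the diet to alter antibiotic use. Only the window needs stating.
- **The effect of GDM on later weight gain is inferred, and only early gain is called a strong predictor.** Both stand. The mediator and consequence roles are plausible but not proven. The objection to the covariate does not need proof of either, since a variable measured mainly after allocation cannot confound a randomised comparison.
- **The size of the bias is unknown and may be small beside sampling error in a pilot.** This stands. The simulated shifts are at most about a third of a standard error, and other coefficients would give other values.
- **Details may be left to a fuller analysis plan.** That does not help here, because the article itself names weight gain as a covariate and defines how it is measured.

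**Conclusion.** The point holds for gestational weight gain in the adjusted logistic model. As defined, it accrues largely after randomisation, is an outcome of the trial, and is a potential mediator. The odds ratio adjusted for it does not estimate the total effect of allocation, which the stated intention-to-treat approach implies.

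No size or direction of bias can be derived from the article. The simulated figures show only that the bias can go either way under the stated assumptions, and they should not be quoted as the bias in this trial. A reader might also infer a general ban on post-randomisation variables in every between-group model. The adherence-adjusted microbiota analyses in Section 2.13.4 ask a different question and are not judged here.

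The plan should be corrected, but because the unadjusted comparison is sound, the fault does not undermine the trial's primary result.

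**What to change.** In Section 2.13, remove weight gain from the adjusted model for the primary outcome and keep it as a secondary outcome under Section 2.13.5. Limit that model to pre-randomisation covariates: age, parity, pre-pregnancy BMI and assisted conception. Include antibiotic use only as reported at baseline. Because Section 2.11 places the baseline questionnaire within one week of enrolment and after randomisation, the wording should say that use before randomisation is meant.

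If the weight-gain pathway is of interest, label that analysis exploratory. It would need weights from around the time of the GDM test. Table 2 schedules anthropometry only at baseline and 36 weeks, so this depends on what the medical records hold.

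The core change is wording. It needs no new data and leaves the sample size, power and significance level as stated. Only the optional pathway analysis could require extra extraction from records.

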#### 2.13.1. Primary Outcome

The primary outcome will be the development of GDM according to the methods and diagnostic criteria outlined in the Queensland Clinical Guidelines [39], which are based on the International Association of Diabetes in Pregnancy Study Group recommendations [40].

#### 2.13.2. Secondary Outcomes

The following items will also be evaluated and reported (Table 2).

#### 2.13.3. Dietary Intake

Long-term maternal dietary intake, measured at baseline, 36 weeks, and 12 weeks, postpartum will be measured using the AES to report on intake of the core food groups, intake according to the Australian Recommended Food Score (ARFS) [41] and energy, fiber, and macronutrient intakes. Short-term (2-week) measures of dietary intake using a version of the Simplified Dietary Questionnaire (SDQ), first modified by Dawson et al. [25] to include prebiotic and probiotic foods will be included and cross-checked against 24 h diet recalls collected at four time points across trimesters 2 and 3. Maternal dietary quality and variety will be evaluated by applying the ARFS and healthful plant-based diet index [42], measured at baseline, trimesters 2 and 3, and 36 weeks gestation. The AES and 24 h dietary recalls will be used to report on the intake of core food groups (servings/day) and daily macro and micronutrients, including energy (kJ), protein (grams), total fat (grams), saturated fat (grams), and fiber (grams). The diet recall data will be entered into an Australian-based program known as FoodWorks [43], which provides the most comprehensive record of foods and food products available in Australia. FoodWorks provides data on energy (kJ), fiber and macro and micronutrient intakes. The modified SDQ will be scored to provide baseline, 36-week and 12-week postpartum data on diet quality and intake of probiotic and prebiotic foods. A Goldberg ratio of ≤0.9 will be used to identify potential under-reporters of energy intakes [44,45].

#### 2.13.4. Gut Microbiota

A between-group difference in microbial alpha diversity (Shannon Diversity Index), inverse Simpson index, Chao1, observed species and phylogenic diversity, relative abundance of operational taxonomic units measured at baseline and 36 weeks, as well as between-sample beta diversity, differences in taxa abundance, and functional capacity between groups and across pregnancy will be analyzed. Differential abundance analysis will be determined at a species level; this will be conducted between groups (intervention and control) and at an individual level. We will be evaluating both the group changes to the microbiota and individual changes from baseline. The influence of the *Healthy Gut Diet* on gut microbiota will be assessed by adjusting for ‘low’ or ‘high’ adherence to the dietary principles using the plant-based index [42] and ARFS [41] as both dichotomous and continuous variables. A sensitivity analysis will be undertaken to understand the impact of antibiotic use during pregnancy on changes to gut microbiota.

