The primary aim of this study is to determine the effectiveness of a dietary intervention called ‘*The Healthy Gut Diet*’ on reducing the diagnosis of GDM in pregnant women with one or more specified risk factors. We hypothesize that there will be fewer women diagnosed with GDM in the intervention group and this effect will be enhanced amongst women who adhere closest to the dietary recommendations. The secondary aim is to understand whether dietary intervention can modulate the gut microbiota compared with the usual care group and if this effect is enhanced in women who closely adhere to the dietary intervention compared to those who are less adherent. The third aim is to compare the maternal and infant outcomes of women enrolled in the dietary intervention and those in the usual care group.

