## 4. Discussion

There is good evidence to suggest that the gut microbiota play a role in the development of GDM. To the best of our knowledge, there have been no dietary interventions aimed at improving ‘gut health’ in pregnancy for the purpose of preventing GDM. One prospective observational study involving 41 women with GDM showed that participants who were adherent to standard GDM nutritional recommendations had better metabolic and inflammatory outcomes and exhibited a significant decrease in the Bacteroides species [22]. To date, there have been no prospective trials used to evaluate the impact of dietary modulation of the gut microbiota and its role in the development of GDM. This pilot RCT will evaluate the effectiveness of the *Healthy Gut Diet* in preventing GDM in women with one or more risk factors and will examine the relationship between dietary intake and the gut microbiota during pregnancy.

Although this is the first RCT to target the gut microbiota in pregnant women with the aim of preventing GDM, there was a recent dietary intervention trial targeting the gut microbiota in pregnant women with the aim of improving maternal diet [25]. In this study, women in the intervention group significantly improved the quality and variety of their diet and their intake of pre- and pro-biotic foods from baseline to follow-up compared to the control group [25]. The impact of such dietary changes on maternal and infant gut microbiota composition for this study has yet to be determined.

Studies investigating changes in the gut microbiota during pregnancy are limited and have yielded mixed results regarding the remodeling of the microbiota during pregnancy. Some studies report dramatic shifts to the gut microbiota across pregnancy trimesters [47,48], whilst others suggest a relatively stable microbial profile [49,50,51]. Yang et al. linked variations in composition and function with GWG, age, residency status, pre-pregnancy BMI, and gestational diseases [51], suggesting that individual heterogeneity is the major force that shapes the microbiota in pregnancy, as opposed to gestation-age variations. By adequately controlling for confounding factors, we anticipate that gestational age variations will have little impact on the result.

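### The microbiota section does not say which contrast decides the comparison with usual care, and it does not state adjustment for the baseline sample

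*Protocol article*

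**What the plan says.** The Introduction frames the microbiota aim as comparative: "The secondary aim is to understand whether dietary intervention can modulate the gut microbiota compared with the usual care group". Section 2.11 collects two stool samples per woman in both arms, at baseline (11 to 18 weeks in Table 2) and at 36 weeks.

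Section 2.13.4 then names these contrasts:

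- a between-group difference in alpha diversity and related measures, with the two sampling times given. This is listed first;
- "differences in taxa abundance, and functional capacity between groups and across pregnancy will be analyzed";
- differential abundance for single species, both between the two arms and for each woman;
- change over time, in a general statement that names no test: "We will be evaluating both the group changes to the microbiota and individual changes from baseline".

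No model is given and no contrast is ranked above another. The only adjustment named for the diet's influence is adherence, alongside a sensitivity analysis on antibiotic use. The baseline microbiota value is not named as a covariate, nor is it ruled out.

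Section 4 reports mixed evidence on natural change in pregnancy. On one side, "Some studies report dramatic shifts to the gut microbiota across pregnancy trimesters"; on the other, some studies find a fairly stable profile. It concludes: "By adequately controlling for confounding factors, we anticipate that gestational age variations will have little impact on the result".

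**The concern.** A change from baseline, in one arm or one woman, has the null hypothesis of no change between early pregnancy and 36 weeks. The aim needs the null hypothesis that the diet makes no difference compared with usual care. The two coincide only if the microbiota would not move without the diet, and section 4 treats that as unsettled.

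The Discussion sentence does not close the gap. Every woman in the intervention arm advances in gestation over the same interval in which she follows the diet, so no covariate can separate the two inside that arm. The concurrent control arm can, because randomisation gives both arms the same expected gestational shift.

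Two things are at stake. A shift caused by pregnancy could be reported as an effect of the diet if within-arm results are given inferential weight. Also, the comparison that does answer the aim may be less precise than the collected data allow.

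**Working it through.** The article gives no SD, effect size or power for any microbiota measure, so there is no figure to reproduce. The calculations below are illustrations under stated assumptions.

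**Inputs.** The target is 120 women (section 2.14) allocated 1:1 (section 2.6), so n = 60 per arm if all provide both samples. Two-sided 5% and 80% power are conventional choices: z = 1.960 and 0.842, sum 2.802. The correlation ρ between baseline and 36-week values is an assumption, shown from 0.3 to 0.8. The outcome SD is set to 1 at both times.

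**1. Precision of three contrasts between arms.** The variance per woman is:

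- 36-week value alone: 1
- change score: 2(1 − ρ)
- 36-week value adjusted for baseline (ANCOVA): 1 − ρ²

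Minimum detectable difference = 2.802 × √(2 × variance / 60). For variance 1 this is 2.802 × 0.1826 = 0.51 SD.

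| ρ | 36-week value | Change score | Baseline-adjusted |
|---|---|---|---|
| 0.3 | 0.51 | 0.60 | 0.49 |
| 0.5 | 0.51 | 0.51 | 0.44 |
| 0.7 | 0.51 | 0.40 | 0.37 |
| 0.8 | 0.51 | 0.32 | 0.31 |

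For example, at ρ = 0.7 the adjusted variance is 1 − 0.49 = 0.51, and 0.511 × √0.51 = 0.365.

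The ordering is general. 1 − ρ² never exceeds 1. Since 1 − ρ² = (1 − ρ)(1 + ρ) and 1 + ρ never exceeds 2, it never exceeds 2(1 − ρ) either. Apart from the one degree of freedom spent on the slope, adjustment is at least as precise as both alternatives. All three contrasts are unbiased under randomisation with complete data.

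**2. What a within-arm test would show with no diet effect.** Suppose both arms drift by d SD through pregnancy alone. The standard error of the mean change in one arm is √(2(1 − ρ)/60): 0.129 at ρ = 0.5 and 0.100 at ρ = 0.7. The probability p that the test is significant in a given arm is Φ(d/SE − 1.96) + Φ(−d/SE − 1.96). The probability that one arm is significant and the other is not is 2p(1 − p).

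| Drift d | p, ρ = 0.5 | Arms disagree, ρ = 0.5 | p, ρ = 0.7 | Arms disagree, ρ = 0.7 |
|---|---|---|---|---|
| 0.2 | 0.34 | 0.45 | 0.52 | 0.50 |
| 0.3 | 0.64 | 0.46 | 0.85 | 0.25 |
| 0.5 | 0.97 | 0.05 | 0.999 | 0.002 |

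With zero drift the within-arm test keeps its 5%. These rates show why such a test cannot decide the aim. They are not error rates of the plan, because the article does not say that such a test will be used as evidence for the diet.

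**The case against.** The strongest reply is that the randomised comparison is planned and comes first, and that a condensed article need not spell out the model for a secondary outcome. Most of this stands. Describing change through pregnancy alongside an arm comparison is legitimate. Covariates of a secondary model are commonly left to the full protocol or the SAP, neither of which is shown.

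Three stronger readings are tempting, and the text does not support them:

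- **That the plan will test change within each arm and read it as a diet effect.** The sentence on group changes names no test. It may mean changes compared between arms, which would already use the baseline sample.
- **That the plan never adjusts for baseline.** It is silent, and silence is not a commitment to leave the covariate out.
- **That a significance test between arms at baseline is planned.** The mention of baseline and 36 weeks may only give the sampling times.

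It is also fair to say that the Discussion sentence is commentary and specifies no analysis, and that the article cites evidence for stability as well as for change.

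What the reply does not remove is that section 2.13.4 lists several contrasts without saying which one answers the aim, and that the Discussion credits confounder control with a task only the control arm can do. An SAP could supply the model, but it would not correct that reasoning in the article.

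**Conclusion.** The point holds as a clarification with a worthwhile gain in precision. It is not a fault in validity. The comparison that answers the aim is present, but it is not identified as the deciding one, and adjustment for a baseline measure already collected is not stated.

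Stating and using that adjustment lowers the minimum detectable difference from 0.51 SD (36-week value or change score) to 0.44 SD at ρ = 0.5. At ρ = 0.7 it falls from 0.51 SD (36-week value) or 0.40 SD (change score) to 0.37 SD. The gain over change scores shrinks as ρ rises.

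These figures assume 60 women per arm with both samples, equal SDs at the two times and a single roughly normal index such as Shannon diversity. With fewer pairs, n per arm, every entry in the first table grows by √(60/n) and the ordering stays the same. The within-arm rates depend further on an assumed drift, and they would matter only if within-arm results were used as evidence for the diet.

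**What to change.** In section 2.13.4:

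- State that inference on the diet's effect rests on the contrast between arms at 36 weeks, adjusted for the same measure at baseline. Use ANCOVA for the alpha-diversity indices. For species and functions, use baseline abundance as a covariate or a group-by-time term.
- Label within-group and individual changes as descriptive.
- State that no significance test between arms will be done at baseline. Randomisation makes that null hypothesis true, so the test says nothing about the diet.

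In section 4, replace the sentence on confounder control with a statement that gestational shifts are handled by comparison with the concurrent control arm.

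The cost is wording only; no samples or visits are added. Section 3 places the analysis after the last data are collected, so the text should be settled before then. The one small downside is that women without a usable baseline sample need a constrained mixed model or simple imputation to stay in the analysis.
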